#### Air pollution

Personal air pollution devices were developed by a local company called Cingularity TEC India Pvt. Ltd. This device measures both PM_2.5_ and CO levels. Personal exposure to PM_2.5_ and CO will be measured for the primary cook two times a week for 24-h hours (total 48-h hours), at baseline, after 6 months and after 12 months.

Ambient air pollution will be measured to control the environmental effects. Two stationary outdoor samples will be placed in the slum for monitoring ambient air pollution. Data will be collected on a continuous basis for 1 year.

#### Questionnaires

Three types of questionnaires will be used. The first questionnaire contains items to map demographic data and to scan for confounders and effect modifiers, including active smoking behaviour of fathers in houses. Pregnancy and type of stove used will be recorded. The data will be used for evaluating exposure to IAP. The information will be collected for all participants at baseline. The second questionnaire assesses symptoms of respiratory morbidity, including cough, phlegm, wheeze, shortness of breath, and symptoms of exposure to air pollutants such as burning eyes and headaches for the primary cook. All other symptoms or conditions considered to be relevant by participants will be recorded. The information will be collected once every 3 months for 1 year. The third questionnaire will include questions regarding changes in behavior, attitude of users and compliance of the primary cook. The questionnaire will be conducted twice a year; at 6 months and after 1 year. All questions will be asked in the local language (Kannada). Questionnaires are displayed in Additional file 1.

#### Interviews

The qualitative semi-structured interview will assess the change in behaviours, attitudes among women and the perceived barriers and facilitators to adoption of the improved cookstove. Interviews will be conducted twice; after 6 months and after 1 year of intervention in a sub-group of the participants who received the intervention. Information will be collected until saturation is reached. All questions will be asked in the local language (Kannada). The interview guide is displayed in Additional file 2.

#### Indicator smoke and soot

In households participating in the qualitative interviews, a standardized piece of white plasterboard will be used to indicate smoke and soot escaped from the stove. The plasterboard of a slightly larger size than the surface covered by the chulha will be placed above the hobs on the wall at the same site to which the stove is installed. The colour of the plasterboard will be used as a qualitative outcome and as educational material for the primary cook.

### Data management

Data for the questionnaires and for the assessment of pneumonia will be collected using a tablet computer with a pre-formatted questionnaire sheet. Data will directly be transferred to an online cloud. The system uses 128-bit SSL secured layer for all data transactions. Both the software subsystem and the database system are secured by this layer. The system can only be accessed through secured username and password. The principle of least privilege, whereby access will be limited to the minimal level that will allow normal functioning, will be followed. Interviews will be audio-recorded and a transcript will be made by fieldworkers after the visits. Data will be stored on a hard-drive. Personal air pollution measurements will be stored on an SD-card in the device and ambient air pollution measurements will be stored on an SD-card and in an online website. Results of spirometry will be transferred to the software winspiroPRO after every visit and will be stored on a hard-drive. Back-ups will be made for all measurements to avoid loss of data. All data collection and storage devices will be password protected. Identifiers, data, and keys will be placed in separate, password protected/encrypted files. Only supervisors and the main researcher will have access to the data files, identifiers, and keys. All data will be stripped of identifiers as soon as possible, and managed by use of a code.

### Data analysis

An intention-to-treat analysis will be conducted in order to ensure external validity of the study and minimize bias. For missing observations, multiple imputation method will be used. Mean (standard deviation) or median (interquartile range IQR, i.e. 25th percentile – 75th percentile) where appropriate will be used for numerical variables, while categorical variables will be presented by number of participants or households (percentage, %). Linear and logistic mixed model analyses will be used to assess the impact of the intervention on numerical and categorical outcomes that are measured repeatedly, respectively. These methods will be used, since they take the correlation between repeated measures into account. For numerical and categorical outcomes that are only measured once, linear and logistic regression analysis will be used. Analyses will include the stratification variable next to grouping variable indicating the treatment allocation (intervention or control) and will be carried out with and without covariates that are related to the outcome, including personal, household and community characteristics. To address potential effect modifiers (X), variables will be added to the model as interaction terms. One potential effect-modifier will be considered, namely active smoking behaviour of fathers in houses.

Interviews will be audio-recorded and be transcribed in Kannada (local language). Transcripts will be translated into English. An inductive coding procedure will be applied, whereby themes derive from emergent patterns in the data. Each transcript will be independently coded by two researchers. Final coding will be based on consensus, with arbitration by a third researcher in the case of disagreement. All transcripts will be manually coded. Ultimately the data will be analysed according to the themes and relevant quotes and text will be consolidated and summarized.

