## Aims

The aim of the present trial is to reduce the levels of household air pollution and improve the respiratory health of women and children by using a locally designed and manufactured improved cook stove. The study design will be a 1:1 randomised controlled intervention trial.

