### Outcomes

The primary outcomes include (1) change in lung function (FEV_1_/FVC) over a period of 1 year as measured by spirometry in the primary cook and (2) incidence of pneumonia over the period of 1 year for children ≤5 years. Secondary outcomes include (1) change in personal PM_2.5_ and CO exposure over a period of 1 year for the primary cook (2) incidence of respiratory symptoms, including cough, phlegm, wheeze and shortness of breath over a period of 1 year for the primary cook (3) prevalence of other related symptoms, including headache and burning eyes over a period of 1 year for the primary cook and (4) change in behaviour and attitudes of user and adoption of the improved cookstove over a period of 1 year as part of a process evaluation.

Primary outcomes, including lung function and pneumonia, were selected based on their prevalence in the specific age-groups. Pneumonia is the leading infectious cause of death in children aged 0–5 years and a substantial part might be attributable to IAP [13]. Lung function will be measured to quantitatively assess the relationship between biomass fuel use and lung function impairment.

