### Sample size

For adult women, the primary outcome is the mean change in FEV_1_/FVC after 12 months compared to baseline. Based on previous research [14], a standardized effect size of 0.562 is expected, which is a medium to large effect size [15]. To detect this effect size with 80% power and a significance level α of 0.05, 51 adults per group (intervention or control) are required. To account for 25% dropout, the required number of adults is equal to 68 per group. As for children younger than or equal to 5 years, the primary outcome is the proportion of children with pneumonia during the study (within 12 months). Assuming a dropout rate of 25% [16], and a proportion (incidence) of 0.50 within the control group [17], 124 children aged 5 or younger within each group (intervention or control) are required to detect a clinically relevant difference in proportions of 0.20 (proportion of 0.30 in intervention group) with 80% power and a significance level α of 0.05. Therefore, a total of at least 250 households with at least one child aged 5 years or younger will be selected in this study. Next to the child aged 5 years or younger (or the randomly selected child aged 5 or younger if there is more than one eligible child), the adult who is responsible for cooking (mother or someone else) will also be asked to participate. This will ensure that the sample size is also large enough for the adults group (see sample size calculation above). Both eligible households with and without children will be included. The study will be extended to other slums, in case the sample size could not be met in Ashrayanagar slum.

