### Data collection

#### Lung function

Change in lung function (FEV_1/_FVC) will be assessed over a period of 1 year as measured by spirometry in the primary cook. Spirometry would be done thrice; at baseline, at 6 months and after 1 year of intervention. Spirometry will be carried out by trained fieldworkers. The highest outcome of three attempts at each point in time will be used in data analysis. A Spirodoc spirometer (MIR, Italy) will be used to assess lung function.

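### The terms named for the lung-function mixed model do not tie the group effect to the powered 12-month change in FEV1/FVC and make no stated use of the baseline value

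*Protocol article*

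**What the plan says.** All references are to the Protocol article.

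- **Outcomes** gives the adult primary outcome as "change in lung function (FEV_1_/FVC) over a period of 1 year as measured by spirometry in the primary cook".
- **Sample size** is more specific: "the primary outcome is the mean change in FEV_1_/FVC after 12 months compared to baseline". It continues: "a standardized effect size of 0.562 is expected", and "To detect this effect size with 80% power and a significance level α of 0.05, 51 adults per group (intervention or control) are required".
- **Data collection, Lung function** sets the visits: "Spirometry would be done thrice; at baseline, at 6 months and after 1 year of intervention". Table 1 agrees.
- **Data analysis** assigns repeatedly measured numerical outcomes to linear mixed models, and outcomes measured once to ordinary regression. On model terms it says: "Analyses will include the stratification variable next to grouping variable indicating the treatment allocation (intervention or control"). Models are to be run with and without covariates describing the person, household and community. One effect modifier is foreseen, smoking by fathers in the home.

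The section names no visit term, group-by-visit term or 12-month contrast. It gives no role to baseline FEV1/FVC. It also does not say whether the response is the ratio at all three visits or the change from baseline at the two follow-up visits.

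**The concern.** A sample size is computed for one quantity, here the arm difference in 12-month change. The analysis should deliver that quantity. In a mixed model over several visits, a group term without a group-by-visit term estimates an average of the arm differences at the visits in the response. That average equals the 12-month difference only in special cases. If the baseline visit is among the responses, one component of the average precedes the stove and has expectation zero under randomisation.

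The article goes as far as naming the model family, the terms to be included and one interaction, but that interaction is not the one that would identify a change between arms. An analyst following the text could arrive at different primary estimates, some of them diluted towards no effect. The baseline ratio, likely a strong predictor of later values, might also go unused.

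**Working it through.** **1. Reproduce the plan's figure.** Inputs from Sample size: effect 0.562, power 80%, α 0.05 (taken as two-sided), equal arms.

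- Normal approximation: n = 2(1.960 + 0.842)² / 0.562² = 49.7, so 50 per arm.
- Two-sample t-test: 50.68, so 51 per arm, as stated.
- Dropout: 51 / 0.75 = 68, as stated.

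The child outcome sets the number of households: 0.50 against 0.30 needs 93 per arm, and 93 / 0.75 = 124, as stated. Since a cook is asked to take part in each of these households, about 93 cooks per arm should complete. Cooks from households without children would add to this.

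**2. What a group main effect estimates.** Let d6 and d12 be the arm differences at 6 and 12 months, with zero expected at baseline. Data are taken as complete, with equal variance and equal correlation ρ between visits.

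| Response | Group term | Full effect by 6 months | Linear growth |
|---|---|---|---|
| FEV1/FVC at 0, 6 and 12 months | (0 + d6 + d12)/3 | 2/3 × 0.562 = 0.375 | 1/2 × 0.562 = 0.281 |
| Change at 6 and 12 months | (d6 + d12)/2 | 0.562 | 3/4 × 0.562 = 0.42 |

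Under these conditions the fractions do not depend on ρ.

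**3. Power on the three-visit reading.** Assume that 0.562 is in units of the SD of change; the article does not say which SD it uses. Then the variance of a single measurement is σ² = 1/[2(1−ρ)], and a woman's three-visit mean has variance σ²(1+2ρ)/3. Power = Φ(δ / [SD × √(2/n)] − 1.96).

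Example with n = 93, ρ = 0.5: SD = √(2/3) = 0.8165; 0.3747 / (0.8165 × 0.1466) = 3.13; power = Φ(1.17) = 88%.

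| ρ (assumed) | 93 per arm, full by 6 months | 93 per arm, linear | 51 per arm, full by 6 months |
|---|---|---|---|
| 0.5 | 88% | 65% | 64% |
| 0.6 | 76% | 52% | 51% |
| 0.7 | 60% | 38% | 37% |
| 0.8 | 41% | 26% | 25% |

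The 12-month change score itself has 97% power at 93 per arm and 81% at 51.

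If 0.562 is instead in units of a single measurement's SD, the three-visit figures at 93 per arm with full effect by 6 months run from 88% to 78% over the same correlations.

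**4. Power on the change-score reading.** The mean of the two changes has variance σ²[(1+ρ)/2 + 1 − 2ρ] = 1.5σ²(1−ρ) = 0.75 in SD-of-change units, so SD = 0.866. At 93 per arm:

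- Constant effect: 0.562 / (0.866 × 0.1466) = 4.43; power = Φ(2.47) = 99%.
- Linear growth: 0.4215 / (0.866 × 0.1466) = 3.32; power = Φ(1.36) = 91%.

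Here the issue is which quantity is estimated, and little power is at risk.

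**5. Gain from baseline adjustment.** The 12-month contrast adjusted for baseline has variance σ²(1−ρ²), against 2σ²(1−ρ) for the change score. The ratio is (1+ρ)/2: 0.75 at ρ = 0.5 and 0.90 at ρ = 0.8, that is, 25% to 10% lower. Power at 93 per arm is then 99% to 98%.

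**The case against.** A reader might infer that the lung-function model contains group and stratum alone and takes baseline as a response, so that the primary effect is certain to be diluted by pre-intervention data. The article does not support that.

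- The sentence on model terms states what analyses will include. It is a minimum list covering every analysis in the trial, it allows covariates related to the outcome, and it excludes neither visit nor baseline FEV1/FVC.
- That baseline is a response is an inference from the visit schedule. The outcome is always described as a change, and change at 6 and 12 months is also a repeatedly measured outcome. On that reading no pre-intervention difference enters the group term.
- The 12-month change alone is one value per woman and could go to the ordinary regression, which would target the powered quantity exactly.
- A condensed article commonly leaves visit terms, covariance structure and the reported contrast to the full protocol or analysis plan, neither of which is shown.
- The steepest power losses belong to 51 women per arm, whereas the household target implies about 93 completers.
- Using a change score instead of baseline adjustment is not an error; it keeps 97% power at 93 per arm.

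All of this stands, and it removes any claim that the planned analysis is known to be wrong. It does not remove the narrower point. The terms that the article names do not single out the 12-month contrast on either mixed-model reading, and choosing among the permitted readings changes the estimate.

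**Conclusion.** The point holds as a gap between endpoint and stated model. The endpoint is the 12-month change; the named terms do not fix that contrast or the role of baseline FEV1/FVC. Without group-by-visit, the group term estimates one half to two thirds of the 12-month effect if all three visits are responses, and three quarters to all of it if change scores are. It equals the powered quantity only on the change-score reading with a constant effect.

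The fractions assume complete data and equal correlation between visits. The power figures further depend on the assumed correlation, effect trajectory and SD unit, so the fall from 97% to 88%-41% at about 93 completers illustrates one reading and does not forecast the trial's power. It would also be wrong to conclude that the sample size is faulty: 51 and 68 per arm both reproduce. This is a free improvement, not a mandatory correction. If the full analysis plan already names the contrast, only the published description needs aligning.

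**What to change.** State one primary model for lung function:

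- response: FEV1/FVC at 6 and 12 months;
- fixed effects: group, visit, group-by-visit, baseline FEV1/FVC and stratum;
- correlation within woman modelled by a random effect or an unstructured covariance;
- primary result: the group contrast at 12 months.

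A constrained longitudinal model, with all three visits as responses and a common baseline mean in the two arms, is an equivalent choice. The wording should say explicitly how baseline enters.

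The cost is a few lines of analysis text, settled before the analyst is unblinded. Spirometry at all three visits is already scheduled, so no data collection or sample size change is needed.

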### Data monitoring

Since the intervention is not a clinical intervention, and does not have adverse effect on the participants, a data monitoring committee has not been formed. However, to review and keep track of the progress of the trial, a clinical advisory committee comprising of relevant experts has been formed. The research team and the members of the clinical advisory committee will meet periodically to review the trial progress. Since the trial does not involve any drugs or medical procedures, the advisory committee is not carrying out any interim analysis.

## Discussion

As far as we know, no studies on improved cookstoves have been conducted in deprived urban areas, especially not in slums, while the effects might be considerably different between rural and urban settings [11]. The findings of this study will assess the effects of an improved cookstove intervention in deprived urban areas. The results may provide evidence for the decrease of air pollution due to improved cookstoves and give critical information about the health effects for both children and women. There can be significant public health implications of the study. First of all, results can directly inform the potential impact of the dissemination of improved cookstoves in (Indian) slums. Secondly, results on the feedback of the improved cookstove can be used to improve the development of the stove. Lastly, the study can be used as a basis for scaling up interventions in other low- and middle income countries in the world.

### Recruitment status participants

Ongoing.

## Abbreviations

CO: Carbon monoxide
FEV_1_: Forced expiratory volume in first second
FVC: Forced vital capacity
IAP: Indoor air pollution
PM: Particular matter
WHO: World Health Organization
